## **SWITCH STUDY PROTOCOL**

### **INTRODUCTION:**

#### **Study Abstract:**

A prospective multicentre study.

Hemodiafiltration can remove middle molecular weight uremic toxins like cytokines with convection method while hemodialysis mostly removes low molecular weight toxins by diffusion method. Hemodiafiltration is thought to cause less inflammation and oxidative stress with ultrapure dialysate and biocompatible membranes. Currently, no studies in pediatric population involve investigating the difference in oxidative stress and inflammation between these dialysis modalities.

The aim of this study is to investigate the alteration of markers of oxidative stress/inflammation between different dialysis modalities ie; hemodialysis versus hemodiafiltration.

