#### **Inclusion criteria:**

- Incident or prevalent HD patients
- Under 18 years old

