## **IDENTIFYING POTENTIAL STUDY SUBJECTS:**

All children on HDF type of dialysis enrolled in HDF-3H study are eligible for participating in the SWITCH study. Potential participants will be approached in the haemodialysis unit or in pre-dialysis CKD clinics by the clinicians who look after them at each site.

All samples will be anonymised using a study code that is known only to the local Principal Investigator and their designated researchers. No persons in the central laboratory will be able to link any biochemical data with individual patients. Samples will be centrifuged and the serum stored at -80°C locked freezers in the local hospitals. Cellular material from blood samples will not be required. Of note, no genetic tests will be performed in the course of this study. Only the serum samples (and not any cellular material) will be batched and transferred on dry ice using designated approved couriers to the Chemical Pathology Unit, Great Ormond Street Hospital, London. At Great Ormond Street Hospital, samples will be stored in locked freezers at -80°C until analysed. At the end of the study period samples will be stored for a further 15 years in -80 freezers at the ICH. The samples will be stored pending ethical approval for another study. [name] will hold custodial rights to all the samples.

All investigations will be performed in a central laboratory at Great Ormond Street Hospital.

These questionnaires will be sent as one 'set' to the local teams to distribute to each family. Completed questionnaires will be sent to the Research Psychotherapist, [name], who will be responsible for ensuring that questionnaires are screened within two weeks of receipt and any concerning information is fed back to the relevant study site as appropriate. Where the questionnaires indicate high levels of clinical concern about either mental health issues or quality of life, a report will be sent to the Chief Investigator, [name], and to the young person's Consultant for further action in order to ensure that any risk or safety planning can take place as required. It will be the responsibility of the local team to manage the psychosocial concerns as they see appropriate and with the help of their local psychosocial teams. All questionnaires will be fully anonymised and only the local PI will be aware of the research code and will be able to identify the patient.

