## **SAMPLES:**

### **Blood sampling:**

- At baseline and 3 months (= end of study)
- 18 ml blood; to be collected from the patient's vascular access just before they start dialysis. Please collect the sample on a mid-week session of dialysis.
- Please collect using the 3H study packs provided.
- Centrifuge and save serum in 10 bottles and store at -80 degrees
- Courier to the central laboratory in Heidelberg (exactly the same as for 3H samples)

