### **TIME-LINE:**

Baseline – At the time of study entry when the first blood samples for the study are collected. This is the same as the bloods for the 3H study.

End of study (3 months of the new dialysis modality) - Assessment will be done at the end of 3 months of HDF

[figure not shown]

[figure not shown]

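### The aim compares hemodialysis with hemodiafiltration, but one sample at entry and one after 3 months of HDF cannot separate an HDF effect from change over time

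*Protocol*

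**What the plan says.** The Study Abstract calls the trial "A prospective multicentre study" and gives the aim as a contrast between modalities: "The aim of this study is to investigate the alteration of markers of oxidative stress/inflammation between different dialysis modalities", the two being hemodialysis and hemodiafiltration. It mentions no randomisation, parallel group or crossover.

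The inclusion criteria admit "Incident or prevalent HD patients". Blood sampling for the markers is fixed as "At baseline and 3 months (= end of study"). The time-line section places baseline at study entry and equates it with the blood draw of the parent HDF-3H study. For the final visit it says: "Assessment will be done at the end of 3 months of HDF". The labels that survive from the time-line diagram show only a time zero and a final visit.

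The section on identifying potential subjects reads differently: "All children on HDF type of dialysis enrolled in HDF-3H study are eligible for participating in the SWITCH study". It also has children approached in pre-dialysis clinics.

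The table in Materials and Method has an HD and an HDF column. It standardises prescriptions across centres and does not set up an HD group to be followed.

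**The concern.** With one value before the switch and one after it, always in that order, modality and elapsed time coincide. A test of month 3 against baseline asks whether the markers changed. It does not ask whether HD and HDF differ, which is the stated aim.

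Some change over 3 months whatever the modality is plausible on the protocol's own terms. Incident patients are eligible, and their markers may still be moving after the start of dialysis. Vascular access, iron treatment and other drugs can also change in the interval. Baseline is tied to study entry and not to the last HD session before the switch, so time on HD may add to the interval.

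This is not a gap that a statistical analysis plan could fill. The aim and the two sampling times are fixed in the protocol, and no model fitted to these two samples alone can separate drift from an HDF effect. At stake is the main sentence of the conclusion: a significant change could be presented as a benefit of HDF when the data show only that markers moved.

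**Working it through.** **1. What the sections provide, side by side**

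| Element | Protocol section | Content |
|---|---|---|
| Contrast | Study Abstract | HD versus HDF |
| Entry population | Inclusion criteria | HD patients, incident or prevalent |
| Entry population | Identifying potential study subjects | Children on HDF in HDF-3H |
| Marker samples | Blood sampling | Two: baseline and 3 months |
| Baseline | Time-line | Study entry; no repeat or run-in |
| Final visit | Time-line | After 3 months of HDF |
| Concurrent HD series, second HD baseline, switch back, staggered switch | None visible | Not provided |

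That baseline is an HD sample is a reading of the inclusion criteria together with the time-line. The protocol never states the modality at baseline, and the second eligibility statement would let in children with no HD value at all.

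**2. Size of the problem (illustration)**

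The protocol states no sample size, alpha, test or effect size, so there is no figure to reproduce. Assumed here: a paired t-test, two-sided 5%, true HDF effect zero, and a background drift of d standard deviations (SD) of the within-child change. The test statistic then follows a noncentral t distribution with n − 1 degrees of freedom and noncentrality d × √n. The rejection rate is P(|T| > t₀.₉₇₅,ₙ₋₁).

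- n = 30, d = 0.2: noncentrality 0.2 × √30 = 1.095, critical value 2.045, rejection rate 18.5%.
- n = 40, d = 0.2: noncentrality 0.2 × √40 = 1.265, critical value 2.023, rejection rate 23.5%.

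Over a range of assumed values:

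| n | d = 0.1 | d = 0.2 | d = 0.3 |
|---|---|---|---|
| 20 | 7.1% | 13.6% | 24.7% |
| 30 | 8.3% | 18.5% | 35.5% |
| 40 | 9.5% | 23.5% | 45.7% |
| 60 | 11.9% | 33.2% | 62.8% |
| 100 | 16.8% | 50.8% | 84.4% |

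The nominal rate is 5%. The bias itself does not depend on n; more children only make it easier to detect and so to misread.

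**3. Regression to the mean**

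If children above an upper baseline quantile q are screened out, and the correlation between visits is ρ, the expected shift at the second visit is (1 − ρ) × φ(z_q) / q, in baseline SD.

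- q = 0.80, ρ = 0.4: 0.6 × 0.280 / 0.80 = +0.21.
- q = 0.95, ρ = 0.8: 0.2 × 0.103 / 0.95 = +0.02.

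The sign is positive. The exclusions (chronic inflammation, active systemic disease) and the infection and inflammation check on the day of assessment select low values. Regression to the mean would therefore tend to raise inflammatory markers and mask a benefit. If the same check applies at both visits, the shift is smaller.

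**4. Cost of a concurrent HD series**

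With SD of the change = 1, two-sided 5% and 80% power, a before-after contrast needs n = ((1.960 + 0.842) / δ)². A comparison of change between two groups needs twice that in each group.

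- δ = 0.5: 31.4, so 32 children before-after; 62.8, so 63 per group, 126 in total.
- δ = 0.8: 13 before-after; 25 per group, 50 in total.

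A drift common to both groups would cancel, at about four times the number of children.

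**The case against.** A within-child switch is a legitimate design. It removes stable differences between children, which a non-randomised HD group would bring back, and it needs far fewer patients in a rare population. The protocol also takes real precautions: the same membrane type, dialyser-area rule and blood flow target for both modalities, pre-dialysis mid-week sampling, and recording of access type, Kt/V, ferritin and drugs, which could serve as covariates. All of this stands, and it is why the point concerns what may be concluded and is no demand for a controlled trial. Adjustment for recorded covariates does not remove an unmeasured time trend that coincides with the switch.

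Three stronger readings are tempting and not supported.

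- That every child is known to be measured once on HD and once on HDF. This is an inference, and the statement on identifying subjects contradicts it.
- That regression to the mean would create a false HDF benefit. No criterion selects children for high markers; the selection runs the other way.
- That the sponsor plans to report the paired change as a modality effect. No test or conclusion is written in the protocol, and an analysis plan may exist. The point is only that these two samples cannot support that attribution.

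The time-line figures are also not shown, so the absence of an HD series rests on the text. The design of HDF-3H is not given in this document; that it follows children on HD is at most implied.

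**Conclusion.** The point holds as a mismatch between the aim and the data the protocol fixes: a between-modality aim, served by one entry sample and one sample after 3 months of HDF. Time and modality are confounded, and no analysis of those samples alone can undo this. Time trend carries the argument; regression to the mean is minor and would tend to act against finding a benefit.

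The error rates of about 19% (n = 30) and 24% (n = 40) are illustrations at an assumed drift of 0.2 SD. Sample size, drift, alpha and test are all assumed, and no passage supports a particular drift. At 0.1 SD the rates are 8% and 10%. The design conclusion does not depend on any of these figures.

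The sponsor should act on it, because the remedy is mainly wording and changes what the trial may claim.

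**What to change.** 1. Restate the aim in the Study Abstract, and the inference to be drawn, as within-child change in markers after switching from HD to HDF. State that the before-after contrast alone will not be attributed to modality. This costs wording only.
2. Reconcile the inclusion criteria (HD patients) with the section on identifying potential subjects (children on HDF), so that every baseline sample is an HD sample, and state the modality at baseline. This is also wording, though it may narrow the pool of eligible children.
3. Only if HDF-3H holds consented paired sera from children who stayed on HD over a similar interval, add a supportive, non-randomised comparison of change, adjusted for baseline marker, interval, access type and centre. The costs are extra assays, a check that consent covers this use, and possible selection bias. It should not replace the within-child analysis.

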#### **Inclusion criteria:**

- Incident or prevalent HD patients
- Under 18 years old

#### **Exclusion criteria:**

- Any systemic disease with active inflammation ie; active period of vasculitis
- Immune deficiency
- Patients using Immunosuppressive drugs
- Any patients with chronic inflammation
- Smokers
- Patients with diabetes
- Patients with pre-existing cardiovascular disease

### **MATERIALS AND METHOD:**

- Type of vascular access (fistula vs central venous catheter), surface area of the dialyzer, blood flow rate, time and frequency of the dialysis sessions. .
- Standardization of the prescription between centers;

|                       | HD                             | HDF                            |
|-----------------------|--------------------------------|--------------------------------|
| Dialyzer              | highflux membranes;
cordiax | highflux membranes;
cordiax |
| Dialyzer surface area | Body surface area $\pm$ %20    | Body surface area $\pm$ %20    |
| Qb                    | $\cong$ 150 ml/dk/m2           | $\cong$ 150 ml/dk/m2           |

|  |              |                                 |
|--|--------------|---------------------------------|
|  | Qb/Qd: 1.5-3 | UF rate: postdilution-
1/3Qb |
|--|--------------|---------------------------------|

## **IDENTIFYING POTENTIAL STUDY SUBJECTS:**

All children on HDF type of dialysis enrolled in HDF-3H study are eligible for participating in the SWITCH study. Potential participants will be approached in the haemodialysis unit or in pre-dialysis CKD clinics by the clinicians who look after them at each site.

All samples will be anonymised using a study code that is known only to the local Principal Investigator and their designated researchers. No persons in the central laboratory will be able to link any biochemical data with individual patients. Samples will be centrifuged and the serum stored at -80°C locked freezers in the local hospitals. Cellular material from blood samples will not be required. Of note, no genetic tests will be performed in the course of this study. Only the serum samples (and not any cellular material) will be batched and transferred on dry ice using designated approved couriers to the Chemical Pathology Unit, Great Ormond Street Hospital, London. At Great Ormond Street Hospital, samples will be stored in locked freezers at -80°C until analysed. At the end of the study period samples will be stored for a further 15 years in -80 freezers at the ICH. The samples will be stored pending ethical approval for another study. [name] will hold custodial rights to all the samples.

All investigations will be performed in a central laboratory at Great Ormond Street Hospital.

These questionnaires will be sent as one 'set' to the local teams to distribute to each family. Completed questionnaires will be sent to the Research Psychotherapist, [name], who will be responsible for ensuring that questionnaires are screened within two weeks of receipt and any concerning information is fed back to the relevant study site as appropriate. Where the questionnaires indicate high levels of clinical concern about either mental health issues or quality of life, a report will be sent to the Chief Investigator, [name], and to the young person's Consultant for further action in order to ensure that any risk or safety planning can take place as required. It will be the responsibility of the local team to manage the psychosocial concerns as they see appropriate and with the help of their local psychosocial teams. All questionnaires will be fully anonymised and only the local PI will be aware of the research code and will be able to identify the patient.

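### The recruitment section makes children already on HDF eligible, although the study needs a baseline on HD before a switch to HDF, so such a child could be enrolled with no HD-versus-HDF contrast

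*Protocol*

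**What the plan says.** The Study Abstract gives the aim: to "investigate the alteration of markers of oxidative stress/inflammation between different dialysis modalities ie; hemodialysis versus hemodiafiltration". The two modalities are treated as distinct.

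Three sections then bear on who enters and what the baseline means:

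- Inclusion criteria: "Incident or prevalent HD patients", under 18 years of age.
- Identifying Potential Study Subjects: "All children on HDF type of dialysis enrolled in HDF-3H study are eligible for participating in the SWITCH study".
- Time-line: the baseline is "At the time of study entry when the first blood samples for the study are collected", with the remark "This is the same as the bloods for the 3H study". The final point is headed "End of study (3 months of the new dialysis modality" and continues "Assessment will be done at the end of 3 months of HDF".

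The Blood Sampling section has two samples per child, at baseline and at 3 months. No parallel group staying on HD is described. The exclusion criteria do not mention current or earlier HDF.

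**The concern.** The protocol describes a switch study: a first sample on one modality, then a second after three months on another. The inclusion criteria and the time-line fit that if the first modality is HD and the second HDF. The recruitment section describes a different child, one who is on HDF when judged eligible.

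Such a child has no new modality to move to and no HD measurement. With two samples and no described comparator, nothing else in the protocol supplies the missing HD value. It cannot be recovered later either, because analysis can only set the pair aside. The study is multicentre, so one site could enrol only children about to switch while another enrols every HDF-3H child on HDF, each following a sentence in the same protocol.

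**Working it through.** The protocol states no sample size, power, significance level, effect size or standard deviation, so there is no figure to reproduce. The check is to trace two children through the text and then to show what mixing them does.

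**Tracing the text**

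| | Child on HD at entry, then switched | Child on HDF at entry |
|---|---|---|
| Inclusion criteria (HD patients) | met | not met, if HD excludes HDF |
| Recruitment sentence (on HDF, in HDF-3H) | not met at entry | met |
| Baseline (study entry, no modality named) | HD sample | HDF sample |
| Final (3 months of new modality, HDF) | HDF sample | HDF sample, but no new modality |
| HD-versus-HDF contrast in the pair | yes | none |

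The child the study needs fails the literal recruitment sentence. The child that sentence admits fails the inclusion criteria and does not fit the time-line. The sections cannot all be followed at once, and no rule says which prevails.

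**Effect of mixing (illustration)**

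Assumptions: the analysis uses the mean within-child change; true switchers have mean change D; a share f of pairs is HDF-to-HDF with zero expected change.

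Mean change over all pairs = (1 − f) × D + f × 0 = (1 − f) × D.

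- f = 10%: 0.90 D
- f = 25%: 0.75 D
- f = 50%: 0.50 D

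To turn this into power, further assume a standardized paired effect d = 0.5 in switchers, a within-group SD of change of 1, two-sided 5% significance, 80% power and a normal approximation. With mixing, the mean is (1 − f)d and the SD is √(1 + f(1 − f)d²).

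N = [(1.960 + 0.842) × SD / mean]², rounded up.

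- f = 0: (2.802 / 0.5)² = 31.4, so N = 32.
- f = 25%: mean = 0.375; SD = √(1 + 0.25 × 0.75 × 0.25) = 1.023; (2.802 × 1.023 / 0.375)² ≈ 58.4, so N = 59.

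Power at the unmixed N is Φ(mean × √N / SD − 1.960).

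| f | N for 80%, d = 0.5 | Power at N = 32 | N for 80%, d = 0.8 | Power at N = 13 |
|---|---|---|---|---|
| 0 | 32 | 80.7% | 13 | 82.2% |
| 10% | 40 | 71.1% | 17 | 71.4% |
| 25% | 59 | 54.5% | 25 | 53.4% |
| 50% | 134 | 27.8% | 57 | 26.7% |

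The proportional shrinkage depends only on f and the zero-change assumption. The N and power columns also rest on an effect size, a significance level and a power that the protocol does not give.

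**The case against.** The best defence is that the recruitment sentence is loosely worded. It may mean children in the HDF group of HDF-3H whose baseline in that study was drawn on HD before they switched. The time-line says the baseline bloods are those of the 3H study, and the Case Report Forms section takes all baseline data from HDF-3H. The formal inclusion list asks for HD patients, and a child with no change of modality cannot complete three months of a new one.

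This stands as a possible reading, and it makes the consequence conditional. It does not remove the contradiction: the protocol never says that the 3H baseline was taken on HD, and no section excludes a child on HDF at entry. If HD in the inclusion criteria were read broadly enough to cover HDF, that section would not secure an HD baseline either.

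A reader might infer three stronger things that the protocol does not support:

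- *That children not yet on dialysis are admitted*, because "Potential participants will be approached in the haemodialysis unit or in pre-dialysis CKD clinics". This says where families are approached and sets no eligibility rule. An incident patient can be approached before starting. The inclusion criteria still require HD patients, and the Blood Sampling section draws both samples from the vascular access before a mid-week dialysis session.
- *That some pairs do lack the contrast.* This depends on such children being enrolled, which the protocol permits but does not show.
- *That the power losses above describe this trial.* They illustrate dilution in general. The comparison is not spelled out here, and a statistical analysis plan, which may exist, was not available.

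**Conclusion.** The point holds as an eligibility contradiction. The recruitment section admits children on HDF, while the inclusion criteria and the time-line imply HD at baseline followed by HDF. That the passages conflict is clear from the text. How many children it affects is unknown.

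The consequence is conditional. Any child enrolled already on HDF gives a pair with no HD-versus-HDF contrast. If such pairs have about zero expected change and are analysed with the rest, the estimated change moves toward zero by their share, for example by 25% at a 25% share. That size rests on the zero-change assumption, an assumed share and a within-child analysis, which the two-sample design makes likely but the protocol does not state.

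It should be corrected before recruitment relies on the sentence, because it governs who enters and what the baseline measures, and a missing HD baseline cannot be restored.

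**What to change.** Reconcile the Inclusion criteria, Identifying Potential Study Subjects and Time-line sections:

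- Replace the recruitment sentence with, for example: *Children enrolled in HDF-3H who are on HD at the Time 0 sample and for whom a switch to HDF is already planned are eligible.*
- State in the Time-line that the baseline sample is taken on HD before the switch. If the 3H sample serves as the baseline, say that it must meet this condition.
- State that any pair whose baseline was taken on HDF is left out of the HD-versus-HDF comparison. The Case Report Forms section already has modality recorded, so such pairs can be identified.

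The cost is a wording amendment and a somewhat narrower pool, limited to the children the study is meant to compare. The recruitment setting and the sentence about benefit to other children on HDF need no change on this account.
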